**Methods:**

Patients with newly diagnosed primary rectal cancer attending surgical clinics at participating centers will be invited to participate in the study. The inclusion criteria for the study are: (1) diagnosis of rectal cancer (0-15 cm) from the anal verge on endoscopy and proximal extent of tumor at or below the sacral promontory on computed tomography (CT) or MRI; (2) meets all MRI criteria for “good prognosis” rectal tumor as defined by the study protocol; (3) 18 years or older; and (4) able to provide written consent. The initial assessment will include: (1) clinical and endoscopic examination of the primary tumor; (2) CT chest, abdomen, and pelvis; and (3) pelvic MRI. All potentially eligible cases will be presented at a multidisciplinary cancer conference to assess for eligibility based on the MRI criteria for “good prognosis” tumor which include: (1) predicted circumferential resection margin (CRM) > 1 mm; (2) definite T2, T2/early T3, or definite T3 tumor with < 5 mm of extramural depth of invasion (EMD); (3) any N0, N1, or N2; and (4) absence of extramural venous invasion (EMVI). All patients fulfilling the MRI criteria for “good prognosis” rectal cancer and the inclusion and exclusion criteria will be invited to participate in the study and proceed to primary surgery. The safety of the MRI criteria will be evaluated by assessing the positive CRM rate and is the primary outcome for the study.

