### Patient Sample and Recruitment, 3-21 Months

Newly diagnosed rectal cancer patients attending surgical clinics at participating centers will be invited to participate in the study.

The *inclusion criteria* for the study are: (1) diagnosis of rectal cancer (0-15 cm) from the anal verge on endoscopy and proximal extent of tumor at or below the sacral promontory on computed tomography (CT) or MRI; (2) meets all MRI criteria for “good prognosis” rectal tumor as defined by study protocol (see Table 2); (3) 18 years or older; and (4) able to provide written consent.

The *exclusion criteria* for the study are: (1) planned abdomino-perineal resection (APR) based on pretreatment assessment; (2) planned local excision based on pretreatment assessment; (3) T1/early (primary) T2 tumor on preoperative imaging (MRI and/or transrectal ultrasound); (4) suspicious extramesorectal lymph nodes on MRI; (5) unable to undergo MRI due to contraindications (ie, claustrophobia, metal fragments, implanted metal devices); (6) metastatic disease (including extramesorectal lymph nodes, carcinomatosis, liver, lung); (7) pregnancy; (8) inflammatory bowel disease; (9) previous pelvic radiation; and (10) more than one primary tumor.

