### Clinical Assessment

A participating surgeon at each center will perform the initial clinical assessment. The surgeon will be responsible for facilitating the standard preoperative assessment that includes: (1) clinical and endoscopic examination of the primary tumor; (2) CT scan of chest, abdomen, and pelvis; and (3) pelvic MRI. The participating surgeon will be responsible for presenting all potentially eligible rectal cancer cases at a multidisciplinary cancer conference (MCC), which must be attended by the surgeon and at least one radiologist and radiation oncologist affiliated with the participating center. Alternatively, if a MCC is not available, the surgeon will be responsible for organizing a multidisciplinary meeting with Radiology and Radiation Oncology Site Leads. At MCC (or multidisciplinary meeting), all patients fulfilling the MRI criteria for “good prognosis” rectal cancer (Table 2) and the inclusion and exclusion criteria will be invited to participate in the study. Figure 1 shows an example of a MRI with a good prognosis tumor. After obtaining consent, this group of patients will proceed to primary surgery.

**Table 2 table2:** MRI criteria for “good prognosis” and “poor prognosis” rectal tumors.

MRI criteria	Good prognosis	Poor prognosis
Predicted CRM	>1 mm (nonthreatened)	≤ 1 mm (threatened)
T-category^a^ and EMD^b^	Definite T2, T2/early T3, or definite T3 with EMD^b^< 5 mm	Definite T3 with EMD^b^ > 5 mm or T4
N^c^-category	Any N0, N1, or N2	Any N0, N1, or N2
EMVI^d^	Absent or equivocal	Present

^a^ Includes, primary tumor, discontinuous tumor nodes, suspicious lymph nodes, and extramural venous invasion; definite T1 and T1/early T2 tumors will be excluded from study protocol

^b^ EMD = extramural depth of invasion

^c^ N=regional lymph nodes

^d^ EMVI = extramural venous invasion

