### Radiologic Assessment

Each MRI will be reported according to the standard protocol for the study [14]. At minimum, the MRI protocol must include high resolution, axial oblique T2 weighted sequences. The MRI report must include: (1) distance to the mesorectal fascia (predicted CRM), (2) T-category (includes, primary tumor, discontinuous tumor nodes, suspicious lymph nodes, and extramural venous invasion; definite T1 and T1/early T2 tumors will be excluded from study protocol) including extramural depth of invasion into the mesorectum (EMD) for all tumors T3 or greater, (3) absence or presence of suspicious lymph nodes, and (4) absence or presence of extramural venous invasion (EMVI). Although presence of suspicious lymph nodes is not a MRI criterion for “good prognosis” tumors, this information will be recorded so that we will be able to assess the accuracy of lymph node assessment on MRI compared to the final pathology since all patients are undergoing primary surgery. If there is any uncertainty regarding these MRI criteria, the reporting radiologist will be instructed to review the MRI with the Site Lead Radiologist to achieve consensus. If consensus is not achieved and/or uncertainty still exists after review by the Site Lead, the reporting radiologist will be asked to contact the Lead Radiologists (LM, MF) for the study for central review. The central study office (SS, EK) will review the MRI reports to ensure that all of these MRI criteria are reported. In the case of missing data, the Radiology Site Lead will be contacted to obtain this data. Participating centers and radiologists will be encouraged to use a synoptic MRI template for the study; however, this is not mandatory for participation in the study [15]. Prior to the start of the study, a Radiology Webinar will be organized to review MRI protocol, definitions, and interpretation of MRI criteria, and educational materials will be provided. In addition, Radiology training sets will be developed and will be required to be successfully completed by participating radiologists.

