## Results

The primary outcome for the study is the positive CRM rate. A positive margin will be defined as any macroscopic or microscopic tumor, discontinuous tumor nodule, or a positive lymph node located within 1 mm of the CRM on final pathologic assessment. We have 30 high volume surgeons at 16 centers participating in this study who see a minimum of 10 new rectal cancer patients over the 18 month time period. Therefore, a minimum of 300 potentially eligible patients will be assessed, and based on the United Kingdom and German studies, it is estimated that 30% (n=90) will be eligible to participate in the study. Assuming an 80% participation rate, it is expected that 75 patients will be recruited over the two year study period.

If seventy-five patients participate, this will provide a 95% confidence interval half-width precision of 6.7% around a point estimate of 10% for the positive CRM rate. If the point estimate for the positive CRM rate is smaller than 10%, the precision around the point estimate will increase.

A Data Safety Monitoring Committee has been organized and will consist of the study statistician, one surgeon, one radiation oncologist, and one pathologist (who are not participating in the study). The study will be stopped if a positive CRM of >10% is reported at any interim assessment, which will occur after every 25 patients accrued in the study.

The secondary outcomes for the study include 2 year LR and disease free survival rates. Descriptive statistics will be used to report: (1) tumor characteristics, (2) positive CRM rate, (3) MRI findings (T-category, N-category, predicted CRM, EMVI), and (4) final pathology (quality of the TME, CRM, T-category, N-category, EMVI). Regression analysis will be performed to assess if any clinical variables are predictive of positive CRM. In addition, comparing the MRI and pathology findings and assessing interobserver agreement for each of the MRI criteria used to identify “good prognosis” tumors will evaluate the accuracy of the MRI interpretation.

This trial is currently recruiting patients.

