### Extramural Venous Invasion

EMVI is a pathologic, microscopic feature that refers to invasion of large vessels deep to the muscularis propria and is a known independent prognostic indicator of distant recurrence and survival in rectal cancer [25]. In previous work, the MERCURY group developed a MRI-based classification for EMVI. Using this classification, the MERCURY group reported a 62% sensitivity and 88% specificity for MRI to detect EMVI using the pathologic specimen as the gold standard and reported fair interrater reliability for accurate detection of EMVI on MRI (kappa=.41, 95% CI 0.31-0.49) [26]. While univariate regression analysis showed that MRI detected EMVI was a negative predictor of recurrence free survival, this was not significant on multivariable regression analysis. While the group had some concern that EMVI was a relatively new MRI criterion for many radiologists, the group acknowledged that EMVI is most often found in the presence of other “poor prognosis” features and seldom the sole MRI criteria used to classify “good” and “poor” prognosis tumors. Therefore, similar to the other MRI criteria, the majority agreed to include MRI predicted EMVI within the context of the study protocol to validate the results of the MERCURY trial and assess the accuracy of MRI detected EMVI by comparing this result to final pathology. The group also agreed that an educational component and training session for participating radiologists be developed as part of the study protocol.

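### All enrolled patients are MRI-negative for threatened margin and definite EMVI, so the planned accuracy comparison can give a negative predictive value but not sensitivity or specificity for these two criteria

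*Protocol article*

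**What the plan says.** The last analysis paragraph of Results states that setting MRI results against pathology, and also "assessing interobserver agreement for each of the MRI criteria used to identify “good prognosis” tumors will evaluate the accuracy of the MRI interpretation". The Discussion section on EMVI makes one part explicit: the study is to "assess the accuracy of MRI detected EMVI by comparing this result to final pathology". The same section cites earlier work with 62% sensitivity, 88% specificity and an interrater kappa of .41.

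Entry depends on the MRI result. Under Patient Sample and Recruitment, a patient must be one who "meets all MRI criteria for “good prognosis” rectal tumor as defined by study protocol (see Table 2"). Table 2 admits only a predicted CRM above 1 mm and, for definite T3 tumors, an extramural depth (EMD) under 5 mm. For EMVI, Table 2 admits "Absent or equivocal", while the abstract and the Discussion Summary admit absent only. Under Clinical Assessment, the patients who meet the criteria and consent go to primary surgery. Pathology in the study comes from them.

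Nodal status is handled differently. Radiologic Assessment says: "Although presence of suspicious lymph nodes is not a MRI criterion for “good prognosis” tumors, this information will be recorded", so that MRI can be compared with final pathology.

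**The concern.** The test whose accuracy is to be evaluated is also the test that decides who enters. For predicted CRM and definite EMVI, only the MRI-negative half of the two-by-two table against pathology is filled. This is complete verification bias. It follows from eligibility, so an analysis plan written later cannot remove it.

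The stake is interpretation. The article says that the EMVI criterion is included to validate the earlier trial's results and to assess accuracy, and it quotes that group's sensitivity and specificity a few lines earlier. A reader would naturally place this study's figures beside them. If sensitivity and specificity were calculated from the enrolled patients, they would reflect the entry rule and not the readers' skill.

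**Working it through.** **The plan's own figure.** No figure is given for the accuracy or agreement analysis. The only precision statement is for the primary outcome: a half-width of 6.7% around 10% with 75 patients. The normal approximation gives 1.96 × √(0.10 × 0.90 / 75) = 6.79%, which agrees apart from rounding. It does not bear on this point.

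**Inputs.** From the Discussion section on EMVI: sensitivity 0.62, specificity 0.88. From Results: n = 75. Assumed, because the article does not give it: pathological EMVI prevalence p of 10%, 20% or 30% before selection on MRI EMVI. Also assumed: equivocal readings are coded as negative, and the cited sensitivity and specificity apply to these patients.

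**Step 1: what selection does to the table.** Per 100 patients at p = 20%:

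| | Pathology EMVI+ | Pathology EMVI− | Enrolled? |
|---|---|---|---|
| MRI+ | 20 × 0.62 = 12.4 | 80 × 0.12 = 9.6 | no |
| MRI− | 20 × 0.38 = 7.6 | 80 × 0.88 = 70.4 | yes |

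Among enrolled patients there are no true positives and no false positives. Calculated sensitivity is 0 / (0 + 7.6) = 0% and specificity is 70.4 / (70.4 + 0) = 100%. These values do not change with the true accuracy.

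**Step 2: what can be estimated.** The false-negative share, which is 1 − negative predictive value (NPV), is

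0.38p / [0.38p + 0.88(1 − p)]

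| p | False-negative share | Expected in 75 | NPV | Approximate 95% half-width |
|---|---|---|---|---|
| 10% | 0.038 / 0.830 = 4.6% | 3.4 | 95.4% | 4.7 points |
| 20% | 0.076 / 0.780 = 9.7% | 7.3 | 90.3% | 6.7 points |
| 30% | 0.114 / 0.730 = 15.6% | 11.7 | 84.4% | 8.2 points |

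As an example with an exact interval, 7 false negatives in 75 give an NPV of 90.7% (95% CI 81.7% to 96.2%).

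**Step 3: the NPV does not give back sensitivity.** Take the 9.7% share, where the ratio of false to true negatives is 7.6 / 70.4 = 0.108, and keep specificity at 0.88.
- At p = 10%, true negatives are 0.792 and false negatives 0.108 × 0.792 = 0.0855. Sensitivity is 1 − 0.0855/0.10, about 15%.
- At p = 20%, sensitivity is 62%.
- At p = 30%, true negatives are 0.616 and false negatives 0.0665. Sensitivity is 1 − 0.0665/0.30, about 78%.

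The same enrolled-patient result therefore fits a sensitivity anywhere from 15% to 78%, depending on a prevalence that the enrolled sample does not reveal.

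**Step 4: CRM.** The same algebra applies. The primary outcome, the positive CRM rate among patients predicted clear on MRI, already is 1 − NPV. With 5 positive margins in 75, for instance, the NPV is 93.3% (exact 95% CI 85.1% to 97.8%).

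**Step 5: the other criteria.**
- MRI N-category is not an entry criterion, so both rows of its table are filled. Suspicious extramesorectal nodes are excluded, so the result concerns mesorectal nodes in patients who meet the other criteria.
- MRI T-category varies among enrolled patients (definite T2, T2/early T3, definite T3), so it can be compared with pathology within that range.
- EMD is cut at 5 mm on the MRI side only. Regression to the mean pushes the MRI-minus-pathology difference downward, so it is not directly comparable with the cited mean difference of −0.05 mm. The documents do not allow the size of this shift to be calculated.

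**Step 6: interobserver agreement.** A simulation used three readings that share a latent trait, with positive-reading prevalence of 20% to 40%, and selected patients who were negative on one reading. Kappa between the other two readings was 0.37 to 0.49 without selection and about 0.26 to 0.32 with it. Agreement remains estimable but is lowered by the restricted range. These values depend on the assumed model.

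**The case against.** The plan does not name sensitivity, specificity or kappa for its own analysis. It promises a comparison, agreement and accuracy, and an NPV is a legitimate part of accuracy. The analysis is also descriptive: the stated secondary outcomes are local recurrence and disease-free survival. This stands in part. It makes the point a correction of a claim and leaves the analysis itself worth doing. It does not rescue accuracy for each criterion, because half of what accuracy means for CRM and EMVI is unobservable here.

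A reader might go further and infer several things that the documents do not support.

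- *Kappa cannot be estimated.* Kappa is zero or undefined only when one of the two ratings is the reading used for selection, or when all-negative MRI is set against pathology. Two independent re-readings of enrolled scans would give a value, although a lowered one.
- *There is no data source for agreement.* The article describes one reporting radiologist, review by consensus when uncertain, and one MRI report sent to the study office. It does not rule out a separate re-reading, and a condensed article commonly leaves such a scheme to the full protocol.
- *Only nodal status can be assessed.* T-category varies on MRI within the sample, and an NPV alone would discard that information.
- *EMVI is constant on MRI.* Under Table 2 equivocal readings may enter. The 0% and 100% results need them to be coded as negative.

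The prevalence range is also open to challenge. The article says that EMVI is most often found with other poor-prognosis features. Those are screened out too, so the upper end of 30% may be too high.

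**Conclusion.** The point holds for predicted CRM and EMVI. No patient with a threatened margin or definite EMVI on MRI has study pathology, so sensitivity and specificity for these criteria cannot be estimated, and nothing from this sample can be compared with the cited 62% and 88%. This follows from the entry rule alone. What can be reported is the NPV. For EMVI, about 5% to 16% of MRI-negative patients, or 3 to 12 of 75, would be positive on pathology. That range rests on the cited test performance, on the assumed prevalence of 10% to 30%, and on equivocal counting as negative.

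Comparisons of T-category and EMD are valid only within the selected range. Any interobserver agreement measured on enrolled scans is likely to understate agreement in unselected patients. The safety question and the positive CRM rate do not depend on any of this.

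**What to change.** 1. In Results and in the Discussion section on EMVI, replace the accuracy claim for predicted CRM and EMVI by the NPV (or false-negative share) with an exact 95% confidence interval. State that sensitivity and specificity for these two criteria cannot be estimated in this design.
2. Reconcile Table 2 with the abstract and the Discussion Summary on whether equivocal EMVI may enter. Then state how equivocal readings are coded in the NPV.
3. Keep sensitivity and specificity for mesorectal N-category.
4. Report T-category and EMD agreement as conditional on the MRI-selected range, with EMD under 5 mm, and say that the EMD difference is not directly comparable with the cited −0.05 mm.
5. State that interobserver agreement measured on enrolled scans is range-restricted and likely to understate agreement in unselected patients. Re-reading excluded patients' scans would ease this. It would not restore sensitivity or specificity, because the study provides no primary-surgery pathology for those patients.

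Item 5 does not require agreement to be taken from the radiology training sets. The article says only that "Radiology training sets will be developed and will be required to be successfully completed by participating radiologists", and it does not describe their case mix.

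The cost is a change of wording and a narrower accuracy claim. Sample size and the primary outcome stay as they are.

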## Discussion

### One Day Investigator’s Meeting

Our team organized a one day investigator’s meeting on June 28, 2013 in Toronto, Ontario, Canada. Colorectal surgeons (n=22), radiation oncologists (n=8), radiologists (n=4), and pathologists (n=1) from high volume rectal cancer centers across Canada attended the meeting. In addition, [name], the principal investigator of the MERCURY trial attended the meeting. The overall objective of the meeting was to: (1) select MRI criteria to identify “good prognosis” rectal tumors (ie, tumors at low risk for LR) eligible for primary surgery, and (2) finalize a protocol to evaluate the safety of using these MRI criteria to select “good prognosis” tumors eligible for primary surgery. Prior to the meeting, the MERCURY and German trial papers, as well as a draft study protocol, were circulated to the participants.

At the meeting, [name] gave a formal presentation of the MERCURY trial results, and the investigative team presented the German trial results. After each presentation, there was a moderated discussion in which the following “good prognosis” MRI criteria were discussed: (1) definition of a threatened CRM in millimeters, (2) T-category and EMD, (3) lymph node assessment, (4) height of tumor, and (5) EMVI.

For the meeting, the following definitions of terms were used. CRM refers to the MRI predicted distance to the mesorectal fascia (MRF). EMD is the extension of the tumor into the perirectal fat beyond the muscularis propria and applies to all T3 and T4 tumors. EMVI is a pathologic, microscopic feature that refers to invasion of large vessels deep to the muscularis propria and is an independent, negative prognostic factor of survival and can be accurately detected on MRI. The highlights of the group discussion for each MRI criteria are detailed below.

### Definition of a Threatened Circumferential Resection Margin

Both the MERCURY and German trial defined a threatened CRM on MRI as < 1 mm, since a CRM < 1 mm has been shown to significantly increase the risk of LR [20,21]. While the German trial defined a threatened CRM as < 1 mm to the primary tumor, discontinuous tumor deposit, EMVI, or suspicious lymph nodes, MERCURY did not include suspicious lymph nodes in their definition of threatened CRM. However, for both studies a positive pathologic margin was considered < 1 mm to the primary tumor, discontinuous tumor deposit, EMVI, or positive lymph nodes. In the MERCURY trial, the majority of the positive pathologic margins were due to the primary tumor. There is also some evidence from the Dutch trial that the LR rate from a positive margin due to a lymph node is significantly lower than a positive margin due to a primary tumor [20]. Overall, our group was concerned about the definition of a threatened margin as < 1 mm, as this was considered very little room for error, especially in a low, anterior tumor in a male pelvis. While an alternative definition of < 5 mm was proposed, the main concern with the use of this definition was that it would result in many more patients being ineligible for the study due to a threatened CRM, and significantly affect recruitment. Furthermore, since a large proportion of these patients would have a negative margin with primary surgery, our group felt that this definition would limit the generalizability of the study. At the end of the discussion, while all of the group members indicated they would not use the < 1 mm definition in their current clinical practice, the majority agreed that they would be willing to evaluate the safety of the < 1 mm definition within the context of the study protocol. The group also felt that use of the < 1 mm definition was important to validate the results of the MERCURY and German trials and the generalizability of this approach.

